### Statistical precision

Given a fixed sample size of at least 148 policy analysts and advisors in the division, a sample-size calculation is not relevant. Instead, we have calculated the level of statistical precision that we can expect given our fixed sample size. We had no mechanism to estimate the intraclass correlation coefficient (ICC) for measurements of the primary outcome for individuals over time. Therefore, we calculated estimates of statistical precision for ICCs of .2, .3, .5, .7, and .8 based on a six-month trial period with 80% power; an estimated standard deviation of 1.0; significance of .05; and 74 participants per study group (total n = 148, which does not include the as yet undefined number of senior policy advisors). Assuming the primary outcome data will be collected from all 148 participants at baseline and at six follow-up points (one per month), the time-averaged detectable difference (in standard deviation units) between the two groups is at best 0.27 (ICC = .2), which increases with successively greater ICCs to 0.30 (ICC = .3), 0.35 (ICC = .5), 0.40 (ICC = .7), and 0.42 (ICC = .8).

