### Outcomes

Measuring the impact of knowledge transfer and exchange (KTE) interventions, such as the evidence service proposed here, poses significant challenges [14]. The ultimate goal of KTE interventions is typically to improve health. However, there is a long chain of potential causal relationships between an evidence service and improved health. For instance, the evidence service may influence the use of research evidence in different stages of the policy-making process, which in turn may influence decisions made by patients and healthcare providers (*e.g.*, healthcare professionals, teams, and institutions), which may in turn influence whether cost-effective programs, services, and drugs get to the patients who need them and have their desired impacts, and which in turn may translate into improved health [15]. Moreover, even the first relationship in this long chain is complicated by the competing influences on the policy-making process, such as institutional constraints within a political system, stakeholder pressure campaigns, values and beliefs held by key decision makers, and external factors such as the state of the economy [16-18]. Similar challenges arise when assessing the impact of KTE interventions, such as guideline-dissemination strategies, on clinical practice and on health [19-21].

Given these challenges, our primary and secondary outcomes for the trial are proxy measures for the use of research evidence in policy making. The primary outcome will be a measure of utilisation that is similar to the one used in a trial of the McMaster Premium Literature Updating Service (PLUS) [12]. Specifically, we will track the mean number of site visits/month/participant across trial groups during each period, that is, the baseline period, intervention period, and crossover period. We will also provide related descriptive measures such as the proportion of users per month in each of the full-serve and self-serve groups; the frequency with which the full monthly update page, systematic review records, and the more detailed documentation for each review (*e.g.*, user-friendly summaries, scientific abstracts, and full-text reports) are accessed; the mean number of minutes per month that participants use the database (with a 'time out' set at 60 minutes); and the number of times the monthly email alerts are forwarded.

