### Data management and analysis

Data will be entered into SPSS 16.0 (IBM Corporation, Somers, NY) after all data collection has been completed. Analyses will be conducted by two members of the research team (SH and [name]), and during the analysis, neither they nor other study investigators will have access to the key linking the participants to their unique identifiers.

We will treat both outcome measures as continuous variables and analyse the change in these measures over time using a two-way mixed-effects linear repeated-measures analysis of variance (ANOVA), with the interaction of intervention by time as the main feature of interest. In addition, we will control for four variables--past workshop attendance, position (policy analyst, senior policy analyst, or senior policy advisor), branch within the division (of which there are six), and number of years working at the MOHLTC--using analysis of covariance. Given the likelihood that the distribution of the outcomes will be skewed, we will transform the data where necessary and possible, which may include adjusting the time period for which we calculate the mean number of site visits/participant (*e.g.*, calculating the mean over two months) if there are insufficient data for analysis. Moreover, as part of a secondary analysis, we will assess whether there is an interaction between each of these variables (entered as a fixed factor) and the outcome measures. We will also qualitatively compare the number of participants in the intervention and control groups that do not complete the follow-up survey and assess whether their baseline characteristics can help to explain their loss to follow-up.

For all analyses, we will use the intention-to-treat principle and report 95% confidence intervals; *p *values equal to or less than .05 (two-tailed) will be considered significant. For the primary outcome measure (mean number of site visits/month/participant), missing data are irrelevant because it is a naturalistic measure. For the secondary outcome measure (obtained through the survey), missing data can be taken into account through the use of a mixed-effects model.

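### The stated detectable differences (0.27 to 0.42 SD) are for a six-month group difference that ignores baseline, not for the intervention-by-time interaction named as the main test; for that test they run the wrong way with the ICC

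*Protocol article*

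**What the plan says.** In the protocol article, Data management and analysis (RCT) plans a two-way mixed-effects repeated-measures ANOVA of change in the outcomes over time, "with the interaction of intervention by time as the main feature of interest". Four variables enter by analysis of covariance: workshop attendance, position, branch and years at the Ministry. The participant's own baseline site use is not among them. The significance rule is that p "values equal to or less than .05 (two-tailed) will be considered significant".

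Statistical precision gives five detectable differences, "based on a six-month trial period with 80% power; an estimated standard deviation of 1.0; significance of .05; and 74 participants per study group". It opens the result with "Assuming the primary outcome data will be collected from all 148 participants at baseline and at six follow-up points (one per month"), and then states that "the time-averaged detectable difference (in standard deviation units) between the two groups is at best 0.27 (ICC = .2"), increasing to 0.30, 0.35, 0.40 and 0.42 for ICCs of .3, .5, .7 and .8. The authors say they had no means of estimating the ICC, which is why they show a range.

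The Abstract places the primary outcome between baseline and the end of the intervention period. The Outcomes section says site visits will be tracked "during each period, that is, the baseline period, intervention period, and crossover period".

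**The concern.** A time-averaged difference between groups and a group-by-time interaction are different estimands with different variances. The first compares levels after baseline, and a high correlation within participants hurts it because repeated months add little new information. The second compares changes from baseline, and a high correlation helps it because the stable part of each participant's use cancels. If the precision figures describe the first while the main test is the second, both the values and their trend with the ICC are attached to the wrong test.

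The sample is fixed, so no recruitment target depends on this. Interpretation does. A null interaction would be read against a detectable difference that the test may not have, and because the ICC is unknown, the reader would take low correlation to be the favourable case when it is the unfavourable one.

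**Working it through.** **Inputs** (Statistical precision, unless noted): n = 74 per arm, SD 1.0, 80% power, alpha .05 (two-tailed, from the analysis section), one baseline and six monthly follow-up points, ICC r = .2, .3, .5, .7, .8. A single ICC implies compound symmetry. The baseline period lasts two months (Abstract; Methods/design), so a two-month baseline is also shown.

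**Formula.** Detectable difference = (1.960 + 0.842) × √(2V/74) = 2.8016 × √(2V/74), where V is the variance per participant of the quantity compared.

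**Step 1: reproduce the stated figures.** For the mean of six follow-up months, V = (1 + 5r)/6. At r = .2, V = 0.333 and the difference is 2.8016 × √(0.667/74) = 0.266. Across the five ICCs the results are 0.266/0.297/0.352/0.399/0.420, which round to all five stated values. Pooling baseline in as a seventh measurement, V = (1 + 6r)/7, gives 0.258 and 0.291 for the first two, which do not match. So the figures make no use of baseline, although the section mentions it.

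**Step 2: the interaction as a single change contrast.** For the follow-up mean minus baseline:
- one baseline month: V = (1 − r)(1 + 1/6)
- mean of two baseline months: V = (1 − r)(1/2 + 1/6)

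At r = .2 these are 0.933 and 0.533, giving 0.445 and 0.336.

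**Step 3: the interaction as an omnibus test.** With one baseline and six months as unordered levels, the interaction has 6 df. For a constant step effect d the noncentrality is (74/2) × d² × (6/7)/(1 − r).

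**Step 4: a baseline-adjusted contrast.** Regressing the follow-up mean on baseline gives:
- one baseline month: V = (1 + 5r)/6 − r²
- two baseline months: V = (1 + 5r)/6 − 2r²/(1 + r)

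| Detectable difference (SD) | r = .2 | .3 | .5 | .7 | .8 |
|---|---|---|---|---|---|
| Stated | 0.27 | 0.30 | 0.35 | 0.40 | 0.42 |
| Change, one baseline month | 0.445 | 0.416 | 0.352 | 0.272 | 0.222 |
| Change, two baseline months | 0.336 | 0.315 | 0.266 | 0.206 | 0.168 |
| Interaction, 6 df | 0.588 | 0.550 | 0.465 | 0.360 | 0.294 |
| Baseline-adjusted, one month | 0.249 | 0.263 | 0.266 | 0.235 | 0.203 |
| Baseline-adjusted, two months | 0.238 | 0.243 | 0.230 | 0.192 | 0.161 |

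**Step 5: power at the stated 0.27 SD, r = .2.**
- Change, one baseline month: Φ(0.27/√(2 × 0.933/74) − 1.960) = 40%.
- Change, two baseline months: Φ(0.27/√(2 × 0.533/74) − 1.960) = 61%.
- 6-df test: noncentrality 37 × 0.0729 × 0.857/0.8 = 2.89, power 20%.

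**Step 6: where the stated figures and the change contrast meet.** One baseline month: 1 + 5r = 7(1 − r), so r = .5. Two months: 1 + 5r = 4(1 − r), so r = 1/3. Below these values the stated figures are optimistic; above them they are pessimistic.

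**Direction.** Every interaction variance is proportional to (1 − r), so its detectable difference falls as the ICC rises, whichever coding of time is used.

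**The case against.** The strongest reply is that the section is arithmetically right for the quantity it names, a time-averaged difference between groups, and never says the figures belong to the interaction. That is true, and the arithmetic is not at fault. But the article gives no other precision figures, and the test it calls the main feature of interest is not the one they describe.

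A second reply is that the size of the gap depends on choices the article leaves open. This also stands. The 20% and 40% powers assume a one-point baseline, and the 20% also assumes unordered monthly levels. With the two-month baseline averaged, power is 61%, and at ICC .3 the gap is small (0.315 against 0.30). With that baseline, three of the five stated values are conservative. None of this changes the direction with the ICC.

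Third, change from baseline is a legitimate randomised comparison, so choosing baseline adjustment over it is a matter of efficiency rather than correction. That is fair, and it is why restating precision for the interaction is offered as the minimum.

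A reader might also infer from the Outcomes wording on three periods that the crossover months enter the primary test, so that a significant interaction could come from the control arm catching up once both arms have the full service. The article does not support this. The Abstract ends the primary outcome at the end of the intervention period, the precision section uses baseline and six follow-up points only, and the Outcomes sentence speaks of tracking visits, not of testing. At most the wording could be clarified.

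**Conclusion.** The mismatch is real. The five stated figures describe a post-baseline group difference, while the planned main test is a change-from-baseline interaction. For that test the detectable difference at ICC .2 is 0.336 to 0.588 SD, depending on baseline length and time coding, rather than 0.27, and power at 0.27 is about 20% to 61% rather than 80%. At ICC .7 and .8 every interaction version computed here detects less than the stated difference, so there the figures understate precision. The description of ICC .2 as the best case is reversed for the planned test.

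It would go too far to call the stated figures wrong in themselves, or to say that the trial lacks power in general: the ICC is unknown and the shortfall is confined to the lower part of the range. These results assume compound symmetry, SD 1.0, 74 per arm, complete data and no gain from the four covariates. Apart from the last, which the article does not mention in this calculation, these are the article's own working assumptions or follow from its use of a single ICC.

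**What to change.** Name one primary contrast with 1 df: the arm difference in mean monthly site visits over the six intervention months, adjusted for each participant's baseline-period use. Fit it by ANCOVA, or by a mixed model with the arms constrained equal at baseline, and keep the four planned covariates. Say whether baseline is one month or the mean of two.

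Then restate the precision paragraph for that test: 0.249/0.263/0.266/0.235/0.203 with one baseline month, or 0.238/0.243/0.230/0.192/0.161 with two. These are smaller than the stated figures at every ICC. Drop the sentence that the detectable difference increases with the ICC: with one baseline month it is largest, among the five values, at ICC .5, and with two at ICC .3.

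If the interaction is kept as the main test, state how time is coded and which baseline is used, and replace the five figures with those for that contrast. Either way, one sentence can confirm that the crossover months lie outside the primary comparison.

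The cost is wording and a recomputed paragraph. Baseline use is already to be collected, so no new data are needed.

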## Qualitative study methods/design

Given that this is the first RCT evaluating a KTE intervention for health-system policy makers (at least to our knowledge) and given the inherent limitations associated with measuring research use as an outcome, we will conduct a qualitative process study after the completion of the trial to explore the RCT findings in greater depth. The qualitative study will explore how and why the evidence service worked (or didn't work), including the role of past workshop attendance and position and the degree of contamination between the intervention and control groups.

### Sample

We will use a mixed-method sequential nested sampling procedure, whereby a larger sample is analysed in one study (RCT) and a subset of the larger sample is selected for further inquiry in the second study [32]. Specifically, 15 participants from each trial arm (n = 30) will be purposively sampled [33,34]. Our sampling criteria include RCT arm (*i.e.*, full-serve or self-serve evidence service), outcomes, past workshop attendance, position, branch within the division, and number of years working at the MOHLTC. We have assumed a 70% response rate (in keeping with our past experience with conducting qualitative studies involving health-system policy makers), which means that we should sample approximately 40 policy analysts and advisors in order to achieve a sample size of 30.

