### Data management and analysis

We will tape and transcribe all interviews, use NVivo 8 (QSR International, Cambridge, MA) for data management, and use a constant comparative method for analysis [35-37]. Specifically, two reviewers will identify themes emerging from each successive wave of four to five interviews and iteratively refine the interview guide and emerging themes until we reach data saturation. This strategy will allow the reviewers to develop and refine codes and broader themes in NVivo 8 that reflect the emerging and increasing levels of nuance that result from the continuous checks that are involved in the constant comparative method [35,37]. The same reviewers will then apply the final analytic framework to all of the interview transcripts and conduct member checking once analysis is completed (*i.e.*, we will send a brief, structured summary of what we learned from the interviews and invite comment on it).

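### At the plan's own 70% response rate, approaching 40 people gives an expected 28 interviews, not 30; the figure should be about 43

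*Protocol article*

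**What the plan says.** The Sample subsection of the qualitative study sets the target: "15 participants from each trial arm (n = 30) will be purposively sampled". It then allows for refusals: "We have assumed a 70% response rate", a rate it attributes to the team's past qualitative work with health-system policy makers. It presents the number to approach as a consequence of these two figures: "we should sample approximately 40 policy analysts and advisors in order to achieve a sample size of 30".

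The subsection does not say how approaches are divided between the arms, whether 40 is a ceiling, or whether people who decline are replaced. The later subsection on qualitative data management and analysis says that interviews are analysed in successive waves of four to five, and that the reviewers will "iteratively refine the interview guide and emerging themes until we reach data saturation".

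**The concern.** A target, a response rate and a number to approach are tied by one simple relation: people approached × response rate = expected interviews. The plan gives all three and says that the third follows from the other two, so it can be checked directly, and it fails. The number to approach exists only to protect the target against refusals. A figure that falls below the target at the assumed rate does not do that job.

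The stake is modest. The interviews are meant to explain how and why the service worked or did not, and to ask about sharing between arms. The 30 people are to be chosen by arm and five further criteria (outcomes, workshop attendance, position, branch and years at the ministry), so each arm's group is already thinly spread. A slightly low figure makes it a little thinner.

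**Working it through.** **Inputs, all from the Sample subsection**
- Target: 30 interviews, 15 per arm
- Response rate: 70%
- Number to approach: approximately 40

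**Step 1. Try to reproduce the plan's figure.** The number to approach is target / response rate = 30/0.70 = 42.86, which rounds up to 43. The stated 40 is not reproduced; it is 3 lower.

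**Step 2. Look for another route to 40.**
- 30 × 1.30 = 39 is close to 40. It would come from adding 30% to the target instead of dividing by 0.70.
- Rounding 42.9 to the nearest ten gives 40.
- 30/0.75 = 40 exactly, but at a 75% response rate.

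The document does not show which route, if any, was taken.

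**Step 3. Work forward from 40.** 40 × 0.70 = 28 expected interviews, and 30 − 28 = 2 short. If the approaches are split evenly (an assumption; no split is stated), each arm has 20 × 0.70 = 14 against a target of 15.

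**Step 4. Find the number that meets the target in expectation.**

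| People approached | Expected interviews at 70% |
|---|---|
| 40 | 28.0 |
| 42 | 29.4 |
| 43 | 30.1 |
| 44 (22 per arm) | 30.8 (15.4 per arm) |

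Taken per arm, 15/0.70 = 21.4, which rounds up to 22 per arm and 44 in all. The answer is therefore 43 on the total, or 44 if each arm is inflated and rounded up separately.

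**The case against.** The best case for leaving the text alone has four parts.

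*The figure is labelled approximate.* The exact answer is 40 to the nearest ten, and the 70% is itself a round number from experience; at 75%, 40 is enough. This stands as a reason to call the matter small. It does not make the figure right. An allowance for refusals that is rounded down gives back part of the protection it was meant to provide, and 70% is the rate the plan chose.

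*The number does not decide when interviewing stops.* Interviews proceed in waves to saturation, and two interviews is less than half of one wave. The team could approach more people from the trial population, and nothing in the text caps approaches at 40. This stands, and it limits the consequence in practice. The stated derivation is still wrong.

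*A purposive qualitative sample has no power calculation to damage.* This stands. Nothing in the trial's own analysis uses this number.

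*The study does not depend on the interviews alone to detect contamination.* This also stands. The Outcomes section and the Discussion add counts of forwarded alerts, and the Discussion adds adjustment for branch. A reader might infer that a shortfall of two interviews would undermine the evidence on contamination; with these other measures in place, the document does not support that.

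**Conclusion.** The recruitment figure is wrong as written, and the error is minor. On the plan's own inputs, 40 approaches yield an expected 28 interviews, two fewer than the 30 claimed (2/30, about 7%). This rests only on the stated 70% and 40. The per-arm figure of 14 also assumes an even split of approaches.

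A reader might go further and infer that the plan will probably miss its quota. A binomial calculation with 40 approaches gives about a 31% chance of at least 30 interviews and about 17% of at least 15 in both arms. Those percentages assume one fixed batch of exactly 40 with independent responses and, for the second, a 20/20 split. The document states none of these, and its wave-by-wave interviewing suggests that recruitment need not stop at one batch. They should not be read as the plan's chance of success. Nor does the discrepancy reach the randomised comparison: outcomes, precision and analysis are unaffected.

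**What to change.** In the Sample subsection, change the number to approach from approximately 40 to approximately 43, or to 44 if 22 are to be approached in each arm. Alternatively, keep 40 and give the expected yield at 70% as about 28 interviews. Either change makes the three figures consistent.

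The cost is one edited number. The first option means three or four more invitations, all to people already in the trial; the Statistical precision section puts the trial at 148 or more. No other part of the document needs to change.

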### Data collection

One-on-one semistructured interviews will be conducted either by telephone or in person (where possible) on participants' views about and experiences with the evidence service, including whether and how they used it (and the degree of 'contamination' between the two arms of the RCT, if any) and why, whether and how it was helpful in their work and why, what aspects were most and least helpful and why, and recommendations for next steps. Potential explanatory factors (for which we will probe) include past workshop attendance, position, branch within the division, and number of years working at the MOHLTC.

